#### Secondary endpoints

ToxicityProgression of treated disease,Time to distant metastasesProgression-free survival,Overall survivalPatient-reported outcomes and quality of life: using the Functional Assessment of Cancer Therapy: Lung (FACT-L) and the EuroQol 5-dimension 5-level (EQ-5D-5L)

#### Statistical design

This study will use a time-to-event continual reassessment method (TITE-CRM). The study design is based on RTOG 0813 and SUNSET trials.

#### Recovery factor levels

Recovery factor levels are described in Tables 1 and 4.

**Table 4 Tab4:** Recovery factor levels

Level	Recovery After 6 Months	Rate/Month	Recovery After 1 Year	Recovery After 3 Years	Recovery After 5 Years	Estimated risk of DLT for initial TITE-CRM model*
−1	3%	+ 0.50%/m	6%	18%	30%	0.034
0	10%	+ 0.50%/m	13%	25%	37%	0.048
1	10%	+ 0.75%/m	15%	33%	51%	0.067
2	15%	+ 0.75%/m	20%	38%	56%	0.094
3	15%	+ 1.00%/m	21%	45%	69%	0.130
4	20%	+ 1.00%/m	26%	50%	74%	0.181
5	20%	+ 1.25%/m	28%	58%	88%	0.252
6	25%	+ 1.40%/m	33%	67%	100%	0.350

Rate/month is additional recovery for every month thereafter

#### Dose assignment procedure

Accrual will start at Level 1 (recovery factor = 10% at 6 months + 0.75% per month thereafter). This recovery factor equation was selected as it translates to approximately 10%/year, which is used in common practice in many Canadian centres, and a lower starting dose may compromise local control for patients enrolled initially. The maximum dose level (Level 6, with 100% recovery at 5 years) was chosen as several studies have reported full-dose thoracic reirradiation. Further dose escalation beyond Level 6 may be investigated in future studies when more is known about recovery time dynamics and organ-specific tissue responses.

Patients will be assigned to recovery factors using the TITE-CRM model (Table 4). The model will use all available information from previously accrued patients to assign the highest dose with a predicted risk of grade 3 toxicity of 35% or less (a similar allowable toxicity level to phase I trials using 3 + 3 designs), with the additional restrictions outlined below.

In the TITE-CRM design, to allow the trial to remain open to accrual without interruption, and in order to use the maximum information from patients already accrued when assigning dose levels, data from patients who have not completed the 1-year follow-up period are weighted according to the proportion of follow-up completed. Weights will range from 0 to 1, with zero denoting no follow-up and 1 denoting 12 months of follow-up (e.g. a patient with 6 months of follow-up will be weighted as 0.5). Any patient with a grade 3–5 toxicity will be weighted as 1, regardless of length of follow-up.

The following restrictions on dose escalation will also be employed:Dose levels may only increase one level between consecutive patients;A patient may not be assigned to a higher dose level unless there is at least 2 years of cumulative observations on patients at the current dose level. This cumulative observation may be divided among several patients (e.g. four patients treated on Level 1 and followed for 6 months each would constitute 24 months of cumulative observation).

In situations where the required recovery allowed by the trial (e.g. 25%) is more than required by the oncologist to deliver the prescribed treatment, those patients will not be enrolled**.**

#### Sample size

In general, TITE-CRM trials require a sample size that is equal to the number of dose levels in the study, multiplied by 6. In this scenario, the sample size will be 48 [28].

#### Statistical analysis

Descriptive statistics will be generated for baseline patient characteristics for all enrolled patients (*n* = 48). Adverse events attributed to treatment will be reported using frequencies and percentages, as maximum reported grade per patient (including proportion of patients with grade ≥ 2 and grade ≥ 3) and separately by individual adverse event categories. Time-to-event endpoints will be estimated using the Kaplan–Meier method for all patients. Median follow-up will be calculated using the reverse Kaplan–Meier method. Quality of life measured using FACT-L scores and utilities measured using the EQ-5D-5L will be stratified by follow-up visit and compared with baseline data using the paired t-test or Wilcoxon signed rank test (in the event these data are non-normally distributed), as appropriate. Linear mixed modelling will be performed to test for changes in quality of life over time, with time as a fixed effect (modelled as continuous) and adjusting for patient number as a random effect (without interaction). Univariable and multivariable Cox proportional hazards and logistic regression will be performed to identify factors predictive of time-to-event endpoints and adverse events of grade ≥ 2 attributed to treatment, respectively. All statistical analysis will be performed using SAS version 9.4 software (SAS Institute, Cary, NC, USA), using 2-sided statistical testing at the 0.05 significance level.

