### Sample size justification and feasibility

In general, TITE-CRM trials require a sample size that is equal to the number of dose levels in the study, multiplied by 6 [28]. In this trial, with 8 dose levels, the sample size will be 48. Given the multi-institutional nature of this study, we estimate that there will be 12–16 patients accrued per year and recruitment will be completed over 36–48 months.

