#### Secondary endpoints

Toxicity, progression of treated disease, distant metastases, progression-free survival, overall survival, patient reported outcomes and quality of life.

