### Patient selection

#### Inclusion criteria

Pathologically (histologically or cytologically) proven diagnosis of malignancy, with disease in the thorax requiring reirradiation for any treatment intent. This may include primary lung cancer of any type, esophageal cancer, recurrences, and/or metastasis from any primary. The intrathoracic disease at the time of enrollment does not itself require a biopsy if a prior biopsy has been obtained at that location or another body site. If the risk of biopsy is unacceptable and there is no prior confirmation of malignancy even at the time of the initial course of radiation, enrollment is permitted provided that the case is discussed at a multidisciplinary tumor board or peer-review rounds.Must have received prior photon thoracic radiotherapy ≥ 6 months agoLife expectancy > 6 months.Eastern Cooperative Oncology Group (ECOG) performance status 0–2Age ≥ 18 yearsThe current radiation course, when added to the previous radiation doses, exceeds the normal tissue constraints used for de novo treatments for esophagus, heart, lungs, trachea, bronchus, great vessels, or brachial plexus. Forgiveness of the previous dose (i.e. reduction of the previous dose in the cumulative dose calculation) is required to meet constraints. Submission of a pre-plan summary showing the estimated accumulation of current and previously delivered doses is required for registration.

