### Follow-up evaluation

Patients will be seen in follow-up as outlined in Appendix 1 (every 3 months in year 1, every 6 months in year 2 then annually to 5 years). At each visit, a history and physical examination will be conducted by the oncologist, and CTCAE version 5.0 study treatment related toxicities recorded. Also, the quality-of-life questionnaire will be completed.

CT chest will be repeated at 3, 6, 12, 18 and 24 months then annually to 5 years. Additional imaging or laboratory investigations may be carried out at the discretion of the oncologist. Pulmonary function tests will be repeated at 6, 12 and 24 months then annually. Following progression of disease, future CT scans are optional.

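### Kaplan-Meier is named for every time-to-event endpoint, which overstates the incidence of distant metastases, and of progression of treated disease if analysed the same way, because death is a competing event

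*Protocol article*

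**What the plan says.** Under Objectives, the secondary endpoints are given as "Toxicity, progression of treated disease, distant metastases, progression-free survival, overall survival, patient reported outcomes and quality of life". The list is repeated under Statistics and sample size, where distant metastases is worded as a time to event. Progression of treated disease is not worded that way in either place.

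The Statistical analysis section sets the estimator for the whole class: "Time-to-event endpoints will be estimated using the Kaplan–Meier method for all patients". It then sets the regression: "Univariable and multivariable Cox proportional hazards and logistic regression will be performed to identify factors predictive of time-to-event endpoints". The article does not mention competing risks or cumulative incidence, and it does not say how death is handled for these two endpoints.

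Two features of the design bear on how often death comes first. Patients are eligible "with disease in the thorax requiring reirradiation for any treatment intent", with a required life expectancy of more than six months. Follow-up visits take place "every 3 months in year 1, every 6 months in year 2 then annually to 5 years".

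**The concern.** A patient who dies without metastasis can no longer develop one. Kaplan-Meier with that death censored treats the patient as someone who would have gone on to have the event at the same rate as those still alive. The resulting curve describes a hypothetical population in which nobody dies first. It does not give the proportion of treated patients whose disease spreads or progresses.

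This matters for how the results will be read. The Background says the trial should support shared decisions about the risks and benefits of reirradiation, and the Dose assignment procedure cites local control when it justifies the starting level. The figure a patient or physician needs is the absolute chance of progression or metastasis, allowing for the chance of dying first. One minus Kaplan-Meier exceeds that figure by an amount that grows with mortality and with time.

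**Working it through.** **The plan's own figure.** The article gives no incidence for either endpoint, so there is no figure of that kind to reproduce. Its sample size statement, "In this trial, with 8 dose levels, the sample size will be 48", reproduces as 8 × 6 = 48. This point does not depend on it.

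**Direction.** At an event time with d events among n at risk, one minus Kaplan-Meier rises by S_KM × d/n, where S_KM falls only at events. The Aalen-Johansen estimate rises by S × d/n, where S falls at events and at deaths. Since S ≤ S_KM, the Kaplan-Meier complement is never below the cumulative incidence. It is strictly above it once any event follows a death. No assumed rate is needed for this.

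**Size.** The document gives no rates, so all rates below are assumptions. With constant yearly hazards p (event) and m (death before the event):

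- One minus Kaplan-Meier, deaths censored: 1 − exp(−p·t)
- Cumulative incidence: p/(p + m) × [1 − exp(−(p + m)·t)]

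For example, with m = 0.5, p = 0.3 and t = 2, the first is 1 − exp(−0.6) = 45.1%. The second is 0.375 × [1 − exp(−1.6)] = 0.375 × 0.798 = 29.9%.

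Results at 2 years:

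| Death hazard m | Event hazard p | 1 − KM | Cumulative incidence | Excess (points) |
|---|---|---|---|---|
| 0.1 | 0.2 | 33.0% | 30.1% | 2.9 |
| 0.3 | 0.2 | 33.0% | 25.3% | 7.7 |
| 0.5 | 0.3 | 45.1% | 29.9% | 15.2 |
| 0.7 | 0.4 | 55.1% | 32.3% | 22.8 |

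**Growth with time.** A second assumed grid uses yearly event risks of 15% and 30% and yearly risks of death before the event from 10% to 40%, each converted to a hazard by −ln(1 − risk). The excess is:

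- 1 year: 0.7 to 6.2 points
- 2 years: 2.6 to 17.1 points
- 5 years: 10.9 to 42.6 points

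**Check at the trial's size.** In 3,000 simulated trials of 48 patients, with 5-year follow-up and both yearly risks at 30%, the mean estimates were:

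| Time | 1 − KM | Aalen-Johansen |
|---|---|---|
| 1 year | 30.0% | 25.5% |
| 2 years | 50.9% | 37.9% |
| 5 years | 82.8% | 48.6% |

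The formulas give 30.0% and 25.5%, 51.0% and 38.0%, and 83.2% and 48.6%, so the two agree.

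**The case against.** **The endpoints are not defined.** Nowhere does the article say that death is excluded as an event, and event and censoring rules are commonly left to a full protocol or analysis plan. This stands as a limit. Even so, both endpoints are listed beside progression-free survival, so counting death as an event would largely duplicate that endpoint. The estimator is also not left open, because the article names it. The wording "progression of treated disease" carries no reference to time, so for that endpoint the point holds only if it is analysed as a time to event.

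**The rates are assumed and the bias may be small.** This also stands. The life-expectancy criterion is an entry minimum and not expected survival, and curative-intent patients can enter. Only deaths before the event compete. At the low-mortality end the excess is about 3 points at 2 years. The standard error of a 30% proportion in 48 patients is √(0.3 × 0.7/48) = 6.6 points. That is sampling error, however, whereas the bias always runs in one direction.

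**A reader might infer that toxicity is inflated in the same way.** It is not. Toxicity is reported as frequencies and percentages, without Kaplan-Meier. With complete follow-up, the crude percentage equals the cumulative incidence at the end of follow-up, since a patient who dies free of the event counts as not having it under both.

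**A reader might also infer that the regressions are wrong.** Cox regression with death censored is already a valid cause-specific hazard model. Logistic regression of grade 2 or higher events is a legitimate model of absolute risk, and replacing it would be a preference.

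**Conclusion.** The concern holds for distant metastases, and for progression of treated disease if it is analysed as a time to event. Naming Kaplan-Meier for these endpoints overstates their incidence. This rests on the natural reading that death is not itself an event for them. Given that reading, the direction is certain. The size is roughly 3 to 23 percentage points at 2 years across the assumed hazards, and it grows with longer follow-up.

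The consequence is confined to descriptive secondary endpoints. Kaplan-Meier is right for overall and progression-free survival. A reader might infer that comparisons between recovery-factor levels would be distorted, but the stated time-to-event estimates pool all patients and no estimate by level is specified. The MTD, the dose assignment and the sample size do not use these estimates.

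**What to change.** In the Statistical analysis section:

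- Keep Kaplan-Meier for overall survival and progression-free survival.
- Estimate time to distant metastases and progression of treated disease by the cumulative incidence function (Aalen-Johansen), with death without the event as a competing event.
- Describe the Cox results for these two endpoints as cause-specific hazards.

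The toxicity percentages and the logistic model need no change. The cost is a change of wording and slightly more analysis work, and reported progression and metastasis rates will be lower than under Kaplan-Meier. Sample size, accrual and data collection stay as they are.

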### Data safety monitoring committee (DSMC)

The DSMC will evaluate AEs on a semi-annual basis. The TITE-CRM model will ensure that the risk of grade 3–5 toxicity doesn’t exceed 35%. However, the DSMC will monitor the risk of related grade 5 toxicity occurring at any time within 1 year of treatment and will track all grade 5 toxicities reported within the 5 year follow-up period. If any dose level sustains 3 related grade 5 toxicities within the first 10 patients on that level, that dose level (and higher) will be closed.

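### Kaplan-Meier for every time-to-event endpoint would overstate the incidence of distant metastases, and of treated-disease progression if analysed as time-to-event, because deaths without the event are censored

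*Protocol article*

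**What the plan says.** The Statistical analysis section fixes one estimator: "Time-to-event endpoints will be estimated using the Kaplan–Meier method for all patients". For regression it adds: "Univariable and multivariable Cox proportional hazards and logistic regression will be performed to identify factors predictive of time-to-event endpoints". It names no other method for time-to-event data. The article nowhere mentions competing risks or cumulative incidence, and gives no rule for a patient who dies before progression or metastasis.

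The Objectives section lists the secondary endpoints as "Toxicity, progression of treated disease, distant metastases, progression-free survival, overall survival, patient reported outcomes and quality of life". The list under Statistics and sample size repeats them and words the metastasis endpoint as a time to event. In both lists, treated-disease progression and distant metastases stand apart from progression-free and overall survival.

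On the population, the inclusion criteria admit patients "with disease in the thorax requiring reirradiation for any treatment intent", including those with metastases. They require a life expectancy above 6 months and ECOG performance status 0 to 2. Follow-up is "every 3 months in year 1, every 6 months in year 2 then annually to 5 years".

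**The concern.** Progression-free survival is a separate endpoint and already counts death. The natural reading is therefore that death is not an event for distant metastases or for treated-disease progression. A Kaplan-Meier analysis of those endpoints then has to censor patients at death, which treats them as still able to have the event later.

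One minus the curve then estimates a net risk: the risk in a hypothetical population in which nobody dies first, and only if death is independent of the event. It does not estimate the proportion of treated patients whose disease progresses or spreads. The estimate is too high whenever patients die without the event and events are still occurring afterwards. The excess grows with follow-up and with mortality.

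What is at stake is how the results are read. The Background says the trial should support shared decision-making, and the Discussion frames reirradiation as a balance between tumour control and harm. A clinician will take the curve as the proportion of patients who failed. The Discussion also expects outcomes to be compared across dose levels; if mortality differs between levels, so does the distortion.

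**Working it through.** **The plan's own figure.** The only design figure nearby is the sample size: "In this trial, with 8 dose levels, the sample size will be 48". It reproduces as 8 × 6 = 48, and nothing below depends on it. The article states no progression, metastasis or death rate to reproduce.

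**Inputs from the article.** Kaplan-Meier for all time-to-event endpoints; the two endpoints listed apart from progression-free and overall survival; follow-up to 5 years.

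**Inputs assumed.** Constant cause-specific hazards; net 2-year event risk of 30%; median time to death *without the event* of 18, 36 or 60 months.

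**Formulas.** With event hazard h_e and hazard of death without the event h_d, per month:

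- Kaplan-Meier with deaths censored: 1 − exp(−h_e·t)
- Cumulative incidence with death competing: [h_e/(h_e + h_d)] × [1 − exp(−(h_e + h_d)·t)]

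**Hazards.** h_e = −ln(0.70)/24 = 0.01486. h_d = ln 2/median = 0.03851, 0.01925 or 0.01155 for 18, 36 or 60 months.

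**Worked case, median 18 months, t = 24.** h_e + h_d = 0.05337 and h_e/(h_e + h_d) = 0.2785. Cumulative incidence = 0.2785 × (1 − exp(−1.281)) = 0.2785 × 0.722 = 20.1%. Kaplan-Meier gives 30.0%.

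| Median time to death without the event | 2 years: Kaplan-Meier v actual | Ratio | 5 years: Kaplan-Meier v actual | Ratio |
|---|---|---|---|---|
| 18 months | 30.0% v 20.1% | 1.49 | 59.0% v 26.7% | 2.21 |
| 36 months | 30.0% v 24.4% | 1.23 | 59.0% v 37.9% | 1.56 |
| 60 months | 30.0% v 26.4% | 1.14 | 59.0% v 44.7% | 1.32 |

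**Other event rates.** With a 12-month net event risk of 15% to 30% and a median time to death without the event of 12 to 60 months, the excess is about 1 to 8 percentage points at 12 months, 3 to 21 at 24 months and 14 to 49 at 60 months.

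**Check at the trial's size.** Simulating 48 patients with a 15% 12-month net risk gave, at 24 months, 27.6% against 15.4% (median 12 months) and 27.7% against 20.4% (median 24 months). The formulas give 27.8% against 15.6% and 27.8% against 20.4%.

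**The case against.** **No mortality rate is given.** This stands. The life-expectancy criterion is a minimum, not an expected survival; performance status must be 0 to 2; curative-intent patients are eligible. That deaths will occur over 5 years is a safe inference from eligibility open to any intent and to metastatic disease. How frequent they will be is not stated. The safety section's closure rule, "If any dose level sustains 3 related grade 5 toxicities within the first 10 patients on that level", shows that fatal toxicity is foreseen, but it is no rate either.

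**A reader might infer a firm overstatement factor.** Setting h_d from a median *overall* survival of 12 to 24 months, with net 2-year risks of 20% to 40%, gives factors of 1.35 to 1.80 at 2 years. The documents do not support that range. Overall survival also counts deaths after progression or metastasis, which do not compete with it. If the death hazard is assumed to rise 3- to 5-fold after the event, the same survival medians give about 1.21 to 1.74. A median time to death without the event of 60 months gives about 1.14.

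**One endpoint is less clearly covered.** Only distant metastases is worded as a time to event. Treating progression of treated disease the same way is an inference from its place in the list. A full protocol might define both endpoints further.

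**Nothing in the trial turns on these endpoints.** Level assignment and the maximally tolerated dose rest on grade 3–5 toxicity, and closure of a level on grade 5 toxicity. This stands and limits the weight of the point.

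**This could be left to the analysis plan.** This does not stand. The article does not leave the estimator open; it names one for all time-to-event endpoints, and an analysis plan that followed it would carry the problem forward.

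**Conclusion.** The point holds for time to distant metastases, and for progression of treated disease if that is analysed as time-to-event. It assumes that death is not counted as an event for these endpoints, which their separation from progression-free survival implies. The direction is then certain as soon as patients die without the event while others go on to have it.

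The size cannot be fixed from the article. In the illustrative case above, the excess is about 4 to 10 percentage points at 2 years and 14 to 32 at 5 years, as the median time to death without the event falls from 60 to 18 months.

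Three broader conclusions that a reader might draw are not supported. Kaplan-Meier is not wrong for overall or progression-free survival. The Cox models are not in error, since a Cox model that censors death estimates a cause-specific hazard. And the problem does not reach the maximally tolerated dose, the TITE-CRM assignments, the safety rule or the 48 patients. It concerns the reporting of two secondary endpoints and is worth correcting before analysis.

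**What to change.** In the Statistical analysis section, limit Kaplan-Meier to overall and progression-free survival. Add a sentence stating that time to distant metastases and progression of treated disease will be estimated by the Aalen-Johansen cumulative incidence function, with death without the event as the competing event. Say explicitly that progression of treated disease is analysed as time-to-event, if that is the intention.

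The Cox models may stay; for these two endpoints, describe the results as cause-specific hazard ratios. That is a reporting note, not a correction.

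The cost is a sentence or two of text. SAS 9.4, which the plan already names, can produce the estimate. No new data, visits or patients are needed.

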**Table Taba:**

	**Before** **Treatment**	**Year 1**	**Year 2**	**Year 3–5**
History and Physical examination	X*	3, 6, 9, 12 mo	18 mo, 24 mo	36, 48, 60 mo
CT chest	X	3, 6, 12 mo	18, 24 mo	36, 48, 60 mo
Pulmonary Function Testing	X	6,12 mo	24 mo	36, 48, 60 mo
Adverse Event Assessment	X	3, 6, 9, 12 mo	18, 24 mo	36, 48, 60 mo
FACT-L and EQ-5D-5L QOL scoring	X	3, 6, 9, 12 mo	18, 24 mo	36, 48, 60 mo

*Abbreviations*: *mo *months

*including weight and extent of weight loss

## Appendix 2

Example calculations for recovery factor

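### The quality-of-life mixed model has one straight line and a random intercept only, so its 0.05 slope test is anti-conservative if patients' trajectories differ, and the line can misread an early dip

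*Protocol article*

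**What the plan says.** The Statistical analysis section of the protocol article plans two QoL analyses.

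- Scores at each visit are to be "stratified by follow-up visit and compared with baseline data using the paired t-test or Wilcoxon signed rank test".
- A mixed model is then fitted to test for a trend across all visits. Its specification has a single time slope and one random term: "with time as a fixed effect (modelled as continuous) and adjusting for patient number as a random effect (without interaction").

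All testing is done "using 2-sided statistical testing at the 0.05 significance level". No patient-specific slope, serial correlation structure or robust standard error is named, and nothing says how the two analyses are to be reconciled if they disagree.

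Follow-up evaluation sets visits "every 3 months in year 1, every 6 months in year 2 then annually to 5 years". The Appendix 1 row "FACT-L and EQ-5D-5L QOL scoring" places both questionnaires at baseline and at 3, 6, 9, 12, 18, 24, 36, 48 and 60 months. That is ten unequally spaced times, nine of them after baseline. QoL is listed among the secondary endpoints.

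**The concern.** A model with a random intercept and a common slope lets patients differ in level but not in direction. Its slope test is valid if all patients truly share one slope and the residuals are independent. If slopes differ, the spread between patients goes into the visit-level residual and is averaged over all visits, as though each visit were a fresh independent observation. The standard error of the mean slope then comes out too small.

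A shared slope is doubtful here. The inclusion criteria admit any treatment intent, primary lung or esophageal cancer, recurrences, and metastases from any primary, with follow-up to five years.

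A straight line over 60 months also cannot represent a fall at 3 to 9 months followed by recovery. Because the early visits sit at the left end of the time axis, such a dip tilts the line upwards. The report could then show a dip in the paired comparisons and an improvement in the model.

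**Working it through.** **The plan's own figure.** Eight dose levels times 6 gives 48, as stated: "In this scenario, the sample size will be 48". This has no bearing on QoL. No QoL effect size, variance or power is given, so nothing further can be reproduced.

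**Inputs.** From the documents: n = 48, the ten visits in Appendix 1, two-sided 0.05. Assumed: intercept SD 15, residual SD σ = 10, true mean slope 0, patient slope SD τ from 0 to 8 points/year, and attrition either none or exponential with median follow-up 36, 18 or 12 months.

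**Closed form with complete data.** In years the visit times sum to 18 (mean 1.8) and their squares sum to 58.125. So Sxx = 58.125 − 10 × 1.8² = 25.725.

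- True SE of the mean slope = √[(τ² + σ²/Sxx)/n] = √[(τ² + 3.887)/48].
- Residual variance as the random-intercept model estimates it, on average = σ² + τ²·Sxx·(n − 1)/(9n − 1) = 100 + 2.805τ².
- Model SE = √[(100 + 2.805τ²)/(48 × 25.725)].
- Approximate type I error = 2·[1 − Φ(1.96 × model SE / true SE)].

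For τ = 3: true SE = √(12.887/48) = 0.52; model SE = √(125.25/1234.8) = 0.32; ratio 0.615; type I error 2·[1 − Φ(1.205)] = 23%.

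| τ (points/year) | True SE | Model SE | Type I, formula | Type I, simulated (800 runs) |
|---|---|---|---|---|
| 0 | 0.28 | 0.28 | 5.0% | 4.5% |
| 1 | 0.32 | 0.29 | 7.6% | 6.1% |
| 2 | 0.41 | 0.30 | 14.7% | 14.2% |
| 3 | 0.52 | 0.32 | 22.8% | 22.1% |
| 5 | 0.78 | 0.37 | 34.8% | 36.1% |
| 8 | 1.19 | 0.48 | 43.3% | 44.8% |

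Formula and simulation agree within Monte Carlo error (about 0.8 points near 5%, up to 1.8 near 50%). With complete data the intercept SD drops out and only τ/σ matters, so the result does not depend on the scale of the instrument.

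**With attrition (simulated).** For τ = 1, 2, 3, 5, 8, type I error is 8%, 12%, 20%, 36%, 52% at median follow-up 18 months, and 8%, 9%, 16%, 28%, 42% at 12 months. With τ = 0 it stays between 4.5% and 6.5% in every attrition setting.

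**Serial correlation alone (τ = 0).** Under the two assumed correlation ranges, type I error is 12% to 21%.

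**With a remedy.** Adding a random slope gives 3% to 8% across all settings. Patient-level robust standard errors give 4% to 7% with no attrition or median follow-up 36 months, and 6% to 12% at 18 or 12 months.

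**Early dip.** Take mean changes of −6, −4 and −2 points at 3, 6 and 9 months and 0 afterwards. The fitted slope with complete data is [(−1.55)(−6) + (−1.30)(−4) + (−1.05)(−2)]/25.725 = 16.6/25.725 = +0.65 points/year. Simulated slopes are +0.65 to +0.93, significant in 25% to 60% of runs. The planned paired test at 3 months detects the dip in 77% to 82% of runs. A random slope alone does not cure the misreading: the slope is still significant in 21% to 57% of runs, because the shape is wrong.

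**The case against.** The strongest reply is that the inflation rests on variances the documents do not give. With no slope variation the planned test holds its level, and at τ = 1 it is only mildly off. The larger settings are demanding: τ = 5 implies a between-patient SD of 25 points by year 5 from slopes alone, and τ = 8 implies 40, against an assumed baseline SD of 15. This stands. A reader might infer that the test simply fails to hold 0.05, or that false QoL claims are likely. The documents support only that the test can be anti-conservative under plausible conditions.

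Second, a reader might infer that early change is lost or that the paired comparisons are a fallback. Neither is so. They are a planned analysis, listed before the model, and cover 3, 6 and 9 months. The fault lies in the model and in its possible conflict with those comparisons.

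Third, a reader might add up the visit-wise tests: nine visits on two instruments give 1 − 0.95^18 = 60%. That assumes 18 independent tests, but the tests share patients and baselines. For nine visits on one instrument the simulation gives 21% to 32%, against 1 − 0.95^9 = 37% under independence. Unadjusted secondary tests are common in a phase I trial with no confirmatory QoL hypothesis, so this is no ground for demoting the paired tests.

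Finally, an exact covariance structure or degrees-of-freedom method is commonly left to an analysis plan that is not shown. That is fair, and none is asked for. Excluding patient-specific slopes, however, is a stated choice.

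**Conclusion.** The point holds in conditional form. The stated model understates the slope's standard error whenever patients' QoL slopes differ or residuals are serially correlated. Simulated type I error is about 5% with no slope variation and roughly 14% to 36% at τ of 2 to 5 points/year, assuming no attrition, residual SD 10 and intercept SD 15. Where the trial will fall in that range cannot be known from the documents. Separately, one straight line can report a transient early dip as improvement, at odds with the planned paired comparisons. The consequence is confined to a secondary endpoint: the MTD, dose assignment and the stopping rule do not use QoL. It is worth correcting because the remedy is a change of wording.

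**What to change.** Amend the sentence on the mixed model in two ways.

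1. Add a patient-specific random slope to the random intercept, or use standard errors that are robust at patient level. Of the two, the random slope held its level better in the simulations with heavy attrition.
2. Enter time as a categorical visit or a non-linear function, and report the estimated change from baseline at each visit with its confidence interval, so that the model and the paired comparisons address the same quantity.

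Both are needed, since the first corrects the standard error and the second corrects the shape. The paired comparisons can stay as planned. The cost is somewhat wider intervals and slightly more analysis work; no change to data collection, visits or sample size is required.
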